### 2.8. *Gongjindan* (GJD)

The GJD group will be orally given 3.75 g of GJD in pill form (product name: Iksu Gongjindan), on an empty stomach every morning for 8 weeks (56 days). This has been determined based on clinical experience within the dose regimen (1 to 3 oral administrations per day) of GJD pills approved by the Ministry of Food and Drug Safety in Korea. The manufacturer, Iksu Pharmaceutical Co. Ltd. (Gwangju, Republic of Korea). obtained Good Manufacturing Practice authorization from the Ministry of Food and Drug Safety in Korea. The GJD pill and its ingredients have also been registered with the same governmental authority.

GJD is composed of six herbs (with country of origin and material standard; KHP, Korean Herbal Pharmacopoeia; KP, Korean Pharmacopoeia): Cervi Parvum (*Cervus elaphus* Linné, family Cervidae, Russia, KHP) 444.33 mg, Angelica Gigas Root (*Angelica gigas* Nakai, family Umbelliferae, Korea, KP) 444.33 mg, Cornus Fruit (*Cornus officinalis* Siebold et Zuccarini, family Cornaceae, China, KP) 444.33 mg, Ginseng (*Panax ginseng* C. A. Meyer, family Araliaceae, Korea, KP) 444.33 mg, Steamed Rehmannia Root (*Rehmannia glutinosa* Liboschitz ex Steudel, family Scrophulariaceae, China, KP) 444.33 mg, and Musk (*Moschus moschiferus* Linné, family Moschidae, Russia, KHP) 74 mg.

After the herbs are weighed, they are pulverized, sterilized, and mixed with the excipient (corn starch 233.33 mg), binders (glycerin 550 mg and suitable amount of honey), and preservative (sodium benzoate 2.25 mg). The mixture is formed into a pill (3.75 g/pill) and covered with gilt paper. Separately packaged and labeled GJD will be directly delivered to the pharmacists of each study site from the pharmaceutical company. A voucher specimen will be retained and kept with the manufacturer.

### 2.9. Placebo

Since there have been no clinical trials to show the effectiveness and/or safety of GJD pills over placebo, we have decided to adopt placebo control for this dizziness trial. Placebo pills will be made by the same pharmaceutical company as the GJD pills. They will be made similar in appearance, taste, and odor to the GJD pills, containing excipients (corn starch 997.76 mg, sodium carboxymethyl cellulose 80 mg, lactose hydrate 1.402 mg, and citric acid hydrate 40 mg), coloring agents (sepia color 10 mg and caramel color 300 mg), binders (glycerin 300 mg and honey 400 mg), flavoring agents, and preservative (sodium benzoate 2.24 mg) with gilt-paper covering. The entire manufacturing process will follow the relevant guidelines of the Korean Ministry of Food and Drug Safety.

The placebo group will be orally given 3.75 g of placebo pill on an empty stomach every morning for 8 weeks (56 days).

### 2.10. Concomitant Medications

All of the concomitant medications will be recorded throughout the trial. No other drugs (betahistine, difenidol, flunarizine, cinnarizine, dimenhydrinate, gingko, meclizine, metoclopramide, scopolamine, pentoxifylline, perphenazine, ergoloid mesylate, droperidol, phenobarbital, prochlorperazine, promethazine, trimethobenzamide, or vertigoheel, etc.) or herbal drugs to manage the symptom of dizziness will not be allowed. Moreover, other therapies for dizziness, like physical therapy, rehabilitation, acupuncture, electroacupuncture, pharmacoacupuncture, moxibustion, cupping, and cognitive-behavioral therapies, will be disallowed during the study.

The following drugs, which can induce drug-related dizziness, will be closely monitored: *α*1-adrenergic antagonists, alcohol, aminoglycosides, anticonvulsants, antidepressants, anti-Parkinson medication, antipsychotics, *β*-blockers, calcium channel blockers, class 1a antiarrhythmics, digitalis glycosides, diuretics, narcotics, oral sulfonylurea, vasodilators, anticoagulants, antidementia agents, antihistamines (sedating), antirheumatic agents, anti-infectives (anti-influenza agents, oral antifungals, quinolones), antithyroid agents, anxiolytics, attention-deficit/hyperactivity disorder agents, cholesterol-lowering agents, bronchodilators, skeletal muscle relaxants, urinary and gastrointestinal antispasmodics, and so on.

### 2.11. Screening Process

After a TKM doctor obtains informed consent from a patient, he/she will go through an extensive screening process for the eligibility decision. Height, weight, body mass index, vital signs (blood pressure, pulse, and body temperature), and electrocardiogram will be measured. Furthermore, blood and urine laboratory tests will be performed, including pregnancy testing. History of medical diseases and drugs will be recorded. If the patient was under administration of any of the drugs disallowed in this study, he/she will be able to participate after a 2-week wash-out period. To rule out untargeted diseases related to chronic dizziness, as listed in the exclusion criteria, we are going to test for CNS abnormalities (deep tendon reflex, Hoffman sign, Babinski sign, ankle clonus, finger to nose, finger to finger, rapid alternating movement, heel to shin, Romberg's test, Brudzinski sign, Kernig sign, Naffziger test, etc.). Additionally, spontaneous, gaze-evoked, positional, and positioning (Dix-Hallpike) nystagmus will be tested for, too. Finally, two TKM doctors will judge if the patient has liver-deficiency pattern/syndrome or not, and those that will receive a consistent diagnosis will be considered to be eligible. The whole process is depicted in Table 1.

### 2.12. Outcomes

#### 2.12.1. Primary Outcome

*Dizziness Handicap Inventory (DHI)*. DHI was developed to evaluate functional, emotional, and physical impairments due to dizziness [26]. This widely used scale for patients with dizziness is a patient-rated outcome (PRO) and has been validated in Korean [27]. The scale consists of 25 items (0, 2, or 4 scores/item, 0–100 scores). The primary endpoint is the mean difference of DHI total score between the baseline and the endpoint of the treatment period. Secondarily, the before-and-after effect of GJD between the baseline and every visit will also be investigated.

#### 2.12.2. Secondary Outcomes

The following outcomes will be evaluated at baseline, mid-term point, and the endpoint of the treatment. The mean differences of each scale score from the baseline and each measurement point will be compared between the GJD and the placebo groups.

*Mean Vertigo Score (MVS)*. MVS is a PRO assessing the intensity of dizziness and has been employed in various clinical trials [28–35]. It includes six items for symptom types and six items for symptom provoking conditions. Patients answer on a scale from 0 (none) to 4 (very strong) and the final score is calculated as the sum divided by 12 (0–4 scores).

*Visual Analogue Scale (VAS)*. The VAS was used in the previous studies on dizziness [36–41]. This scale consists of a 10 cm line, where 0 represents “not dizzy at all” and 10 “dizziest I can imagine being.”

*Dizziness Frequency*. Patients will be asked how many episodes of dizziness they experience. The frequency will be scored as 0 (none), 1 (less than once a month), 2 (1–4 episodes/month), 3 (1–4 episodes/week), 4 (once a day), or 5 (more than twice a day), as per the notation used in the previous studies [38–41].

*Berg Balance Scale (BBS)*. The BBS was originally developed for elderly patients with balance impairment; however, it has been used to assess overall balance ability regardless of age. Its reliability [42, 43], validity [44], and sensitivity [45] have been verified and it has been validated in Korean [46]. Patients will be asked to perform 14 tasks and each task will be evaluated separately.

*Fatigue Severity Scale (FSS)*. GJD is widely administered to patients with chronic fatigue. In this study, we are going to assess the patients' fatigue level with the FSS. This 7-point Likert scale (nine items, 9–63 score range) is a PRO and it has been validated [47].

*Global Perceived Effect (GPE)*. GPE is a validated scale evaluating a patient's perception of symptom worsening or improvement around a specific timepoint [48]. This scale has also been used in clinical studies on dizziness [38, 40, 41], and it consists of seven options (1 for completely recovered to 7 for worst ever).

Based on the previous study showing that the patients with dizziness can become markedly depressed and anxious [49], the following scales will also be included.

*Korean Version of Beck's Depression Inventory (K-BDI)*. The K-BDI is a PRO evaluating the severity of depression with 21 items (0 to 3/points, 63 points in total). The Korean version of this scale has been validated [50, 51].

*State-Trait Anxiety Inventory (STAI)*. The STAI assesses the level of anxiety in the subdomains of state and trait. Each subdomain includes 20 items and each item has the options of 1–4 points (20–80 scores/subdomain). Its reliability and validity have been shown [52].

*Qi Blood Yin Yang-Deficiency Questionnaire (QBYY-Q)*. GJD is a herbal medication prescribed to patients with liver-deficiency pattern/syndrome in TKM. Therefore, we assumed that the level of deficiency pattern/syndrome could vary between groups at the end of the intervention. QBYY-Q is a PRO to evaluate the severity of qi-, blood-, yin-, and yang-deficiency pattern/syndrome [53, 54]. A previous clinical study on chronic fatigue demonstrated the reliability and validity of this scale [55]. The scale consists of 32 items and each item is rated from 0 to 3 points.

#### 2.12.3. Blinding Assessment

This is a double-blind clinical trial with placebo control. Both study participants and TKM doctors will remain blind until the end of the trial. At the end of treatment of each participant, they will be asked in which group they think they belonged to, the GJD group, placebo group, or unknown, and the new Blinding Index (BI) will be calculated following [56]. The index score varies within 1 (complete lack of blinding), 0 (consistent with perfect blinding), or −1 (guessed they were in the opposite group).

#### 2.12.4. Safety Assessment

The AEs will be monitored during the whole treatment period. The following adverse reactions are expected: anorexia, discomfort feeling of stomach area, nausea, vomiting, diarrhea, or rash on skins. The intensity and frequency of each episode will be recorded. Moreover, laboratory tests will be performed at baseline and the endpoint. Complete blood cell tests (red blood cell, hemoglobin, hematocrit, platelet, and white blood cell), serum biochemical tests (creatinine, BUN, ALT, AST, and glucose), and urinalysis (pH, specific gravity, glucose, ketone, red blood cell, nitrate, total protein, bilirubin, urobilinogen, and white blood cell) will be performed. If serious AEs occur, postmanagement will be properly conducted.

#### 2.12.5. Cost-Effectiveness Assessment

The EuroQoL five dimensions' questionnaire (EQ-5D), consisting of two parts, that is, EQ-5D-5L and EQ VAS, will be used to assess quality of life, based on which QALY will be calculated. The Korean version of EQ-5D scale has been studied on its validity and reliability [57]. Also, direct costs (medical and nonmedical expenses) incurred in treating dizziness during the treatment (8 weeks) and follow-up (up to 12 months from randomization) periods will be investigated (Table 1). Medical fee signifies the cost paid in hospitals or clinics. Nonmedical fee signifies transportation and time costs that patients would incur for dizziness treatment. Based on the calculated QALY and fees, the incremental cost-effectiveness ratio (ICER) will be estimated (ICER = Δ  cost/Δ effectiveness). The ICER signifies the amount of cost necessary to improve by 1 unit of effectiveness.

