### 2.1. Objectives and Hypothesis

The primary objective of this study is to evaluate the effect of GJD administration for 8 weeks, compared to placebo, on chronic dizziness (MD, psychogenic dizziness, or dizziness of unknown cause). The alternative hypothesis is that the mean difference between Dizziness Handicap Inventory (DHI) scores at baseline and endpoint in the GJD group will not be equal to that in the placebo group.

Additionally, the changes in dizziness severity and frequency will be evaluated with validated scales. Further, the levels of fatigue, depression, anxiety, and quality of life (QoL) will be compared between the two groups posttreatment. The safety of GJD administration will be examined based on laboratory tests and adverse events (AEs). Finally, the cost-effectiveness of GJD will be evaluated with quality-adjusted life years (QALY).

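### The ICER in section 2.12.5 divides the cost of treating dizziness by a generic EQ-5D QALY, so an adverse reaction affects the denominator while the cost of treating it is left out of the numerator

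*Protocol article*

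**What the plan says.** Section 2.12.5 of the protocol article defines both parts of the ratio.

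- **Numerator.** The costs are "direct costs (medical and nonmedical expenses) incurred in treating dizziness during the treatment (8 weeks", and then over follow-up to 12 months from randomization. Two definitions come next. For medical costs: "Medical fee signifies the cost paid in hospitals or clinics". Nonmedical costs are "transportation and time costs that patients would incur for dizziness treatment".
- **Denominator.** The EQ-5D "will be used to assess quality of life, based on which QALY will be calculated". No restriction to dizziness is stated.
- **Ratio.** "Based on the calculated QALY and fees, the incremental cost-effectiveness ratio (ICER) will be estimated", as the cost difference over the effectiveness difference.

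Two other sections bear on this. Section 2.12.4 states: "The following adverse reactions are expected: anorexia, discomfort feeling of stomach area, nausea, vomiting, diarrhea, or rash on skins". Of these events it says "The intensity and frequency of each episode will be recorded"; it mentions no resource use or cost. Section 2.1 adds that "the levels of fatigue, depression, anxiety, and quality of life (QoL) will be compared between the two groups posttreatment", so effects beyond dizziness are part of what the trial looks for.

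**The concern.** A ratio of costs to QALYs is easiest to interpret when both parts cover the same consequences of treatment. Here the cost side is tied to one condition and the effect side is general. If a participant has a stomach reaction or a rash and seeks care for it, the loss of quality of life can lower the QALY total, but the bill is not a cost of treating dizziness as the section words it. The omission matters most for adverse reactions, because these are consequences of the intervention being valued and the article itself expects them.

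The stake is the cost-effectiveness aim, which is named in the abstract, the introduction and section 2.1, and for which section 2.2 extends follow-up to 12 months. If the cost form asks only about dizziness, the missing costs cannot be reconstructed in full afterwards.

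**Working it through.** The article states no cost, QALY or ICER figure, so there is none to reproduce. The check compares scopes first and then asks how the ratio responds.

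**1. Scope, side by side**

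- Dizziness care: cost counted; health effect in the QALY.
- Care for adverse reactions: cost not counted as worded; health effect in the QALY.
- Care for fatigue, low mood or anxiety: cost counted only if it qualifies as dizziness treatment; health effect in the QALY.

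The medical-cost definition names no condition, but it explains a term in a sentence already limited to dizziness. The nonmedical definition repeats the limit.

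**2. Could other data fill the gap?** From Table 1:

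- Adverse events are scheduled at V3 to V6.
- Concomitant medication is scheduled at V1 to V6.
- Cost information is scheduled at V3 to V9, seven visits.
- At V7 to V9 only the EQ-5D and cost information are scheduled.

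Drugs taken for a reaction during the 8 weeks would therefore be on record, but not visit, transport or time costs. After V6 the cost form is the only source.

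**3. Formula.** Write ΔC_D, ΔC_AE and ΔC_O for the between-arm differences (GJD minus placebo) in the cost of dizziness care, adverse-event care and other care, and ΔQ for the QALY difference.

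- ICER as written = ΔC_D / ΔQ
- ICER with full scope = (ΔC_D + ΔC_AE + ΔC_O) / ΔQ
- Relative error = ΔC_D / (ΔC_D + ΔC_AE + ΔC_O) − 1; ΔQ cancels
- Absolute error in size = |ΔC_AE + ΔC_O| / |ΔQ|

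**4. Relative error under assumed inputs.** Set ΔC_D = 100 units. None of these values comes from the documents.

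- ΔC_AE = 0, ΔC_O = 0: 100/100 − 1 = 0%
- ΔC_AE = 10, ΔC_O = 0: 100/110 − 1 = −9.1%
- ΔC_AE = 30, ΔC_O = 0: 100/130 − 1 = −23.1%
- ΔC_AE = 30, ΔC_O = −30: 100/100 − 1 = 0%
- ΔC_AE = 0, ΔC_O = −30: 100/70 − 1 = +42.9%

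Higher adverse-event costs with GJD make the ratio as written too low. Savings on other care make it too high. The two can cancel.

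**5. Absolute scale, also assumed.** For each 10,000 KRW per participant of omitted net cost difference:

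- ΔQ = 0.005: 10,000/0.005 = 2.0 million KRW per QALY
- ΔQ = 0.05 × 8/52 = 0.0077 (utility gain of 0.05 held for 8 weeks): about 1.3 million
- ΔQ = 0.02: 0.5 million
- ΔQ = 0.05 × 1 year = 0.05 (the same gain held for 12 months): 0.2 million

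The shift depends heavily on how long a gain lasts, which the documents do not say.

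**The case against.** There is a serious case on the other side.

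- **A reader might infer that the ratio is biased as a matter of fact.** The documents do not show this. Bias needs a between-arm difference in the omitted costs, and the omissions can push in opposite directions. This objection stands and limits the point to a possible bias of unknown sign.
- **A reader might infer that all mood and anxiety care is excluded.** The introduction says psychogenic dizziness is treated with antianxiety agents or antidepressants and cognitive-behavioral therapy, and psychogenic dizziness is one of the three enrolled diagnoses. For those participants such care can be dizziness treatment. This stands too. What remains is that section 2.12.5 gives no rule for deciding.
- **The wording may be wider than it looks.** The medical-cost definition names no condition, and care for a reaction to the study pill might be read as part of treating dizziness. The full protocol may say more about the cost form. This has some force, but the limit is stated twice in the article and nothing there adds adverse-event care. If a wider scope was meant, the same rewording settles it.
- **Condition-related costing reduces noise.** With 39 randomized per group, costs of unrelated illness could swamp the difference. This stands against making all-cause cost the base case. It does not weigh much against adding adverse-event care, which follows from the intervention.

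**Conclusion.** The point holds in a limited form. As written, the cost of treating adverse reactions lies outside the ICER numerator while their health effect lies inside the denominator, so the ICER can be biased if those costs differ between arms. Size and net direction cannot be derived from the documents. The range of −23.1% to +42.9% rests on assumed omitted costs of up to 30% of the dizziness cost difference, and the KRW shifts rest on assumed QALY differences; neither is an estimate for this trial.

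A reader might go further and infer that the cost-effectiveness aim cannot be answered at all. That is not supported: the error is zero if the omitted costs are equal between arms or offset each other, and the article gives no expected ICER or decision threshold against which a shift could be judged. Cost-effectiveness is an additional aim, and the primary DHI comparison is untouched. The change is worth making because it is cheap and because costs not asked about at the visits cannot be fully recovered later.

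**What to change.** Reword section 2.12.5 as follows.

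1. The cost form at V3 to V9 records each health-care contact with its reason: dizziness, adverse event or other.
2. The base-case cost is dizziness-related care plus treatment of adverse events, in both arms. State whether anxiety or mood care in participants with psychogenic dizziness counts as dizziness-related.
3. The ICER is also reported with dizziness-only costs and with all-cause direct costs, as sensitivity analyses.

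The price is one extra field on a form already scheduled at seven visits, a few sentences of text, a slightly longer form for participants and a slightly noisier cost difference. The all-cause analysis will be noisier still, which is why it stays a sensitivity analysis.

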### 2.13. Sample Size Calculation

To calculate the effect size, we used a preceding RCT on acupuncture therapy for MD with DHI assessment, as there have been no clinical studies for GJD effectiveness in chronic dizziness [58]. The null hypothesis is that *μ*_GJD_ = *μ*_placebo_, while the alternative hypothesis is *μ*_GJD_ ≠ *μ*_placebo_, where *μ* denotes the mean difference of DHI score between the baseline and endpoint. With the mean difference (−3.63) and the standard deviation (4.84), under the assumption of correlation coefficient (0.1), the sample size was calculated as 29 per group (two-sided, *α* = 0.05 and 1 − *β* = 0.8). Therefore, we are going to recruit 78 participants for both groups (39 per group) under a 25% anticipated dropout rate.

### 2.14. Statistical Analysis

The primary and secondary variables for the effect assessments will be statistically analyzed by analysis of covariance (ANCOVA) or rank ANCOVA with group and site as covariates. If any demographic characteristics show significant difference between groups, those variables will also be used as covariates. When there is a significant interaction between diagnosis (MD, psychogenic dizziness, or dizziness of unknown cause) and group, subgroup analysis will be performed.

The confidence interval (CI) of BI will be addressed and blinding will be deemed successful when the CI includes the zero value. For safety assessment, the chi-squared test or Fisher's exact test will be performed with the proportions of AEs, while lab results will be compared between groups by chi-squared test (proportions of abnormal results) or McNemar's test (before-and-after comparison within a group). An independent statistician ([name]) will analyze any data with a significance level of 0.05 (two-sided) with SAS 9.4 software (SAS Institute Inc.).

The primary analysis will be performed with the full analysis set, which is defined as the group of participants who were prescribed at least once or more the GJD or placebo pills and for whom DHI was evaluated more than once. The missing data will be imputed with the last observation carried forward method. The per protocol set will be additionally analyzed, which includes only the participants who complete all the scheduled visits. We are going to include any participants who took at least one pill of the study drugs for the safety assessment.

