## Abstract

This study protocol aims to explore the effectiveness, safety, and cost-effectiveness of a herbal medication,* Gongjindan* (GJD), in patients with chronic dizziness. This will be a prospective, multicenter, randomized, double-blind, placebo-controlled, parallel-group, clinical trial. Seventy-eight patients diagnosed with Meniere's disease, psychogenic dizziness, or dizziness of unknown cause will be randomized and allocated to either a GJD or a placebo group in a 1 : 1 ratio. Participants will be orally given 3.75 g GJD or placebo in pill form once a day for 56 days. The primary outcome measure will be the Dizziness Handicap Inventory score. Secondary outcome measures will be as follows: severity (mean vertigo scale and visual analogue scale) and frequency of dizziness, balance function (Berg Balance Scale), fatigue (Fatigue Severity Scale) and deficiency pattern/syndrome (qi blood yin yang-deficiency questionnaire) levels, and depression (Korean version of Beck's Depression Inventory) and anxiety (State-Trait Anxiety Inventory) levels. To assess safety, adverse events, including laboratory test results, will be monitored. Further, the incremental cost-effectiveness ratio will be calculated based on quality-adjusted life years (from the EuroQoL five dimensions' questionnaire) and medical expenses. Data will be statistically analyzed at a significance level of 0.05 (two-sided). This trial is registered with ClinicalTrials.gov NCT03219515, in July 2017.

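### The model for DHI change lists group and site but not baseline DHI, so precision is lost; how much depends on what the unlabelled 0.1 and 4.84 in section 2.13 refer to

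*Protocol article*

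**What the plan says.** All places are in the protocol article.

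- **Endpoint.** Section 2.12.1: "The primary endpoint is the mean difference of DHI total score between the baseline and the endpoint of the treatment period". Sections 2.1 and 2.13 also work with the change; in 2.13 the parameter μ "denotes the mean difference of DHI score between the baseline and endpoint".
- **Model.** Section 2.14 uses "analysis of covariance (ANCOVA) or rank ANCOVA with group and site as covariates" for the primary and the secondary variables alike.
- **Rule for adding terms.** Section 2.14: "If any demographic characteristics show significant difference between groups, those variables will also be used as covariates". No other route for adding a covariate is given.
- **Sample size.** Section 2.13 takes a difference of −3.63 and an SD of 4.84 as inputs and works "under the assumption of correlation coefficient (0.1". It arrives at 29 per group for 80% power at a two-sided α of 0.05, raised to 39 per group for 25% dropout. The text does not say which two quantities the correlation links, or whether the SD belongs to the change or to a single time point.
- **Data collected.** Table 1 has DHI at V1 (screening), V2 (day 0) and every treatment visit up to V6. A DHI of at least 24 at baseline is an entry criterion (section 2.5).

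**The concern.** Group and site are both categorical. With only these two terms, the analysis called ANCOVA has no continuous covariate and amounts to a two-way ANOVA of change scores. The rule for extra terms does not help: DHI is a clinical score and not a demographic characteristic, so baseline DHI stays out even if the arms visibly differ on it.

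A raw change score subtracts the whole baseline value, whereas regression on baseline subtracts only the part that predicts the endpoint. The weaker the baseline-endpoint correlation, the more noise the raw change carries. If the 0.1 in section 2.13 is that correlation, the loss is large. Precision of the primary comparison is at stake, and so is the extent to which a chance baseline difference between two small arms carries through into the result.

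**Working it through.** **Inputs.** Difference 3.63, SD 4.84, correlation 0.1, two-sided α 0.05, power 0.80, 29 per group and 25% dropout, all from section 2.13. Equal SDs at baseline and endpoint are an assumption, because the article gives no separate SDs. Power figures use the two-sample t-test unless noted and ignore the few degrees of freedom spent on site and baseline.

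**Step 1: reproduce the plan's figure.** For a two-sample comparison with SD 4.84, the normal approximation gives 2 × [4.84 × (1.960 + 0.842) / 3.63]² = 27.9, so 28 per group. The exact t calculation gives 29, with power 0.801. Then 29 / 0.75 = 38.7, so 39 per group and 78 in total. The stated figures reproduce.

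**Step 2: variance with and without baseline.** With equal SD σ at both times and correlation ρ:

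- change score, no baseline term: 2σ²(1 − ρ)
- baseline-adjusted: σ²(1 − ρ²)
- ratio: 2 / (1 + ρ)

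At ρ = 0.1 the ratio is 1.8 / 0.99 = 1.82, or √1.82 = 1.35 on the standard error. A simulation with 29 per group and four sites gave 1.80.

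**Step 3: sensitivity.** With k = baseline SD / endpoint SD, the ratio is (k² + 1 − 2ρk) / (1 − ρ²).

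| Assumption | Variance ratio |
|---|---|
| ρ = 0.1, k = 1 | 1.82 |
| ρ = 0.1, k = 0.75 | 1.41 / 0.99 = 1.43 |
| ρ = 0.1, k = 1.25 | 2.31 / 0.99 = 2.34 |
| ρ = 0.3, k = 1 | 1.54 |
| ρ = 0.5, k = 1 | 1.33 |
| ρ = 0.7, k = 1 | 1.18 |
| 0.1 is the correlation of baseline with change | 1 / (1 − 0.1²) = 1.01 |

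**Step 4: power at 29 per group, by meaning of 4.84** (ρ = 0.1, k = 1).

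*Reading A: 4.84 is the SD of change.* Then σ = 4.84 / √1.8 = 3.61 and the adjusted residual SD is 3.61 × √0.99 = 3.59. The standard error of the group difference falls from 4.84 × √(2/29) = 1.27 to 3.59 × √(2/29) = 0.94. Power goes from 0.80 to about 0.97. With adjustment, 17 per group would give 80%.

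*Reading B: 4.84 is the SD at a single time point.* The SD of change is 4.84 × √1.8 = 6.49. The unadjusted change analysis then has power 0.55 (0.57 by normal approximation) and would need 51-52 per group. The adjusted residual SD is 4.84 × √0.99 = 4.82, which gives power of about 0.81.

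The adjusted calculation under reading B also returns 29 per group (28 by normal approximation). The stated 29 therefore cannot show which reading was meant.

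**Step 5: chance imbalance.** With equal SDs, a baseline difference between arms passes into the unadjusted difference in change at a rate of 1 − ρ, or 90% at ρ = 0.1. Under reading A, an imbalance of 0.3 SD is 0.3 × 3.61 = 1.08 points and moves the estimate by 0.9 × 1.08 = 0.97 points, which is 27% of 3.63. The standard error of a baseline difference at 29 per group is √(2/29) = 0.26 SD, so an imbalance of that size is only 0.3 / 0.26, about 1.1 standard errors.

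**The case against.** - **The figure of 1.82 rests on assumptions.** A reader might infer that the plan itself commits to a near doubling of the variance. It does not. Section 2.13 never says what the 0.1 correlates, and no separate SDs are given. The entry threshold of 24 could narrow the baseline spread, which would pull the ratio towards 1.43. This stands. The reading under which almost nothing is lost is strained, though: with equal SDs and a baseline-endpoint correlation of 0.1, baseline and change correlate at −√(0.9/2) = −0.67, far from 0.1 in size.
- **The analysis is valid as written.** A reader might infer that leaving out baseline biases the treatment effect, or that regression to the mean does. The documents do not support that. Under randomisation the change-score comparison is unbiased, its standard error already allows for chance imbalance, and regression to the mean acts on both arms alike. The shift in step 5 is conditional on an observed imbalance. This stands.
- **The trial need not be underpowered.** A reader might infer that the omission costs planned power. Under reading A it does not, because 29 per group gives 80% without baseline. Only reading B produces a shortfall, and the text does not establish reading B. The single-time-point SD of 3.61 implied by reading A looks small for a 0-100 scale scored in steps of 2, so the point values in step 5 should be taken lightly.
- **The article is a condensed account.** It calls group a covariate and names ANCOVA for a list with no continuous term, so the sentence may be incomplete and not a deliberate choice. That is possible. But it prints both a covariate list and a rule for extending it, and baseline DHI is in neither, so this is more than detail left to a fuller document.

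**Conclusion.** The point holds as a loss of precision. As printed, the primary model omits a covariate that is measured in every participant before treatment.

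The size is conditional. The variance factor is 1.82 if 0.1 is the baseline-endpoint correlation and the SDs are equal. It is between 1.18 and 1.54 at correlations from 0.7 down to 0.3, 1.43 at correlation 0.1 with a baseline SD of 0.75 of the endpoint SD, and about 1.01 if 0.1 links baseline to change. The consequence for power turns on whether 4.84 is the SD of change (80% against about 97%) or a single-time-point SD (about 55-57% against about 80%).

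Validity is not in question: the unadjusted estimate is unbiased over randomisation, though it carries chance baseline imbalance that adjustment would remove. This is a free improvement, and not a defect that invalidates the planned analysis.

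**What to change.** 1. Prespecify the primary model as DHI at V6 (or change to V6) = group + site + baseline DHI, and name V2 as the baseline, since DHI is also taken at V1. The estimated group effect is the same whether V6 or change is the response.
2. Use the same form for each secondary scale that has a baseline value, with that scale's own V2 score. GPE is measured only at V6 (Table 1), so no baseline term applies to it.
3. State in section 2.13 which two quantities the 0.1 correlates and whether 4.84 is the SD of change or of a single time point, so that the sample size can be checked against the model actually used.

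The cost is a few lines of wording and one degree of freedom per model. No new data are needed. The change should be fixed before unblinding, so that the choice of covariate cannot depend on the results.
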